## Abstract

**Background:**

Medications are an effective intervention for managing and preventing health problems but their benefit can be undermined by non-adherence or adverse drug events (ADEs). Since these issues may be interconnected, efforts to improve non-adherence should also include reduction of ADEs. We have developed the ISTOP-ADE system (Information Systems-enabled Outreach for Preventing Adverse Drug Events), which enables timely monitoring and managing of ADEs. The objectives of this study are to determine whether the ISTOP-ADE system, compared to routine care, will reduce: a) the probability of discontinuing the use of prognosis-altering medications; b) the probability of a patient experiencing a severe ADE; c) the proportion of patients experiencing ADEs, preventable ADEs and ameliorable ADEs; and d) health services utilization.

**Methods/design:**

We will randomly assign 2,200 adult ambulatory patients in the province of Québec who have been prescribed an incident medication for the management or prevention of a chronic health condition, to routine care or the ISTOP-ADE system. The ISTOP-ADE system consists of an interactive voice response system (IVRS) paired with pharmacist support. The IVRS will call patients at 3 and 17 days post-prescription to determine if they are experiencing any problems and connect them with a pharmacist when required or desired by the patient. We will evaluate medication persistence at 180 days and health-care utilization using provincial administrative data. Two blinded physicians will ascertain ADE status through a case review.

**Discussion:**

We expect the ISTOP-ADE intervention to be feasible and to improve the quality of patient care through improved medication adherence, reduced ADE duration and reduced number of ADEs resulting in an emergency department or inpatient encounter. This in turn could lower health-care utilization, saving costs and lowering the burden on emergency departments and family practices. The success of ISTOP-ADE would present opportunities to implement this intervention through health systems, health insurance agents and commercial pharmacies.

**Trial registration:**

ClinicalTrials.gov Identifier: NCT02059044. Date registered: 10 January 2014.

## Background

Medications are an effective intervention for managing and preventing many acute and chronic health-care problems. Their benefit is commonly reduced by non-adherence, in which patients either do not take or stop taking the medication as prescribed, or by adverse drug events (ADEs), in which patients experience side effects of the medications. These issues are interrelated. Some patients do not take their medication due to their fear of an impending ADE, while others stop taking the medication because of an ADE. Therefore, efforts to increase adherence should include efforts to target ADE reduction specifically.

To address these concerns, we have developed the Information Systems-enabled Outreach for Preventing ADEs (ISTOP-ADE) system (protocol version 1, 1 March 2012). The ISTOP-ADE system consists of a set of business processes supported by a technology infrastructure. The information technology is designed to connect providers to patients and includes an electronic health record system, a clinical data repository and an interactive voice response system (IVRS). This system enables timely monitoring of patients for ADEs and couples it with an effective arm to manage ADEs if, and when, they occur.

We recently established the feasibility and acceptability of the ISTOP-ADE system in a prospective cohort study. The pilot study included 628 patients who were prescribed an incident prescription. The ISTOP-ADE system successfully contacted 90% of patients. Important measures of the system’s effectiveness included the identification of 45% of ADEs, 50% of all potential ADEs and 30% of primary non-adherence episodes. In terms of potential benefits, it positively influenced the management of 42% of all medication-related problems. In terms of acceptability, almost all patients found it easy to use and understand and reported they would use the system again if it was provided to them. Physicians and pharmacists also supported the system
[1, 2]. While these results are favorable, a controlled clinical trial in which patients are randomly assigned to the ISTOP-ADE system or routine care is required to determine the system’s effectiveness. We therefore designed this study.

## Methods/design

This study has been approved by the McGill Institutional Review Board (A01-B02-02A) and the Ottawa Health Science Network Research Ethics Board (20130285-01H).

### Setting

This research will occur during ambulatory care in the province of Québec, Canada. We will study prescriptions in patients receiving primary care from a selected group of physicians using the Medical Office of the 21st Century (MOXXI) electronic health record system. MOXXI was developed by the McGill University’s Clinical and Health Informatics Research Group. It is currently used by over 100 primary care physicians in Montréal and Québec City. The MOXXI system is linked to the provincial insurance company, Régie de l’assurance maladie du Québec (RAMQ), resulting in an electronic medical record that displays a drug profile of prescribed as well as dispensed drugs, emergency department visits and hospitalizations in the past 12 months, a list of active and past health problems, and an electronic prescribing tool. Data stored by MOXXI have been used by the McGill research team for medical research in the past
[3, 4].

### Primary objective

The primary objective is to determine whether the ISTOP-ADE system, compared to routine care, will reduce the probability of discontinuing the use of prognosis-altering medications in patients prescribed an incident medication to manage or prevent a chronic health condition.

### Secondary objectives

Determine whether the ISTOP-ADE system, compared to routine care, will reduce the probability of a patient experiencing a severe ADE (defined as an ADE lasting at least 7 days or causing an emergency department visit).Determine whether the ISTOP-ADE system, compared to routine care, will reduce the proportion of patients experiencing ADEs, preventable ADEs and ameliorable ADEs.Determine whether the ISTOP-ADE system, compared to routine care, will reduce health services utilization (comprising physician visits, emergency department encounters and hospitalizations) at 12 months following an incident prescription.Measure the costs associated with the ISTOP-ADE system.

### Participants

This study will include French- and English-speaking adult patients (age >18) who receive a high-risk incident prescription, use RAMQ insurance to pay for medications and are followed by a physician who has consented to be in the MOXXI research network. We will exclude patients if their physicians do not deem them appropriate for study inclusion.

We define high-risk prescriptions as medications commonly used to prevent progression or complications related to the following conditions: congestive heart failure, hypertension, dyslipidaemia, type 2 diabetes mellitus, coronary artery disease, cerebrovascular disease, atrial fibrillation, chronic renal failure, chronic obstructive lung disease, depression, dementia, autoimmune conditions, seizures, and chronic pain. The selected medications (Table 
1) have an important impact on outcomes or they have been shown to have a high frequency of ADEs
[5, 6]. We will consider prescriptions as ‘incident’ if the patient had not received a prior prescription for that medication in the 12 months preceding the index event.

**Table 1 Tab1:** **Included diseases and drug classes for the ISTOP-ADE study**

Disease entity	Drug classes included
Congestive heart failure	Angiotensin-converting enzyme inhibitors, angiotensin II receptor antagonists, hydralazine, mineralocorticoid (aldosterone) receptor antagonists, nitrate, diuretic, cardiac glycoside, β-adrenergic blocking agents
Diabetes mellitus	Sulfonylurea/insulin secretagogue, biguanide, A-glucosidase inhibitor thiazolidinedione, incretin therapy (dipeptidyl peptidase-4 inhibitor), insulin
Hypertension	β-adrenergic blocking agents, diuretic, calcium-channel blocking agents, angiotensin-converting enzyme inhibitors, angiotensin II receptor antagonists, nitrate, central α-agonists
Coronary artery disease	β-adrenergic blocking agents, statin, calcium-channel blocking agents, angiotensin-converting enzyme inhibitors, angiotensin II receptor antagonists, nitrate, acetylsalicylic acid, clopidogrel
Dyslipidemia	Statin, cholestyramine resin, fibric acid derivatives, niacin derivative, cholesterol absorption inhibitor
Cerebrovascular disease	Acetylsalicylic acid, clopidogrel, statin, dypiramidole
Atrial fibrillation	β-adrenergic blocking agents, cardiac glycoside, class III anti-arrhythmics, class Ic anti-arrhythmics, calcium-channel blocking agents, vitamin K antagonist, thrombin inhibitor, Acetylsalicylic acid
Chronic kidney disease	Angiotensin-converting enzyme inhibitors, angiotensin II receptor antagonists, thiazide diuretic, β-adrenergic blocking agents, calcium-channel blocking agents
Chronic obstructive pulmonary disease	Short-acting bronchodilators, long-acting bronchodilators, phosphodiesterase type-4 inhibitors, combination inhaled corticosteroids and long-acting bronchodilators, theophylline
Depression	Serotonin-specific reuptake inhibitors, serotonin-norepinephrine reuptake inhibitors, monoamine oxidase inhibitors, tricyclic antidepressants, quetiapine, bupropion, trazodone, mirtazapine
Dementia	Parasympathomimetic (cholinergic)
Autoimmune conditions	Corticosteroids
Seizures, chronic pain	Anticonvulsants

Participants will be enrolled in the ISTOP-ADE study if they have an incident prescription for a high-risk medication. We define high-risk prescriptions as medications commonly used to prevent progression or complications related to key conditions (disease entities). The selected drug classes have an important impact on outcomes or they have been shown to have a high frequency of ADEs.

### Eligibility assessment and consent

When a physician uses MOXXI to prescribe a new medication for a patient, a pop-up window will appear on their computer screen to indicate the patient’s eligibility. This pop-up window will prompt the doctor to inform the patient of the study, confirm their eligibility and seek consent. We will obtain informed consent from each participant. If the patient consents, the physician will confirm the patient’s phone number, preferred language and preferred time of day to be called. If the physician deems the patient ineligible or the patient does not consent, then the reason will be captured in MOXXI using a standard classification.

### Randomization

The unit of analysis for the study is the individual patient, each of whom we will randomly assign to the intervention or control arms using a computer algorithm. We will perform stratified randomization at the physician practice level with block sizes of four. We will only randomize patients once a physician confirms the patient’s eligibility for enrolment. We will update the ISTOP-ADE system with the patient’s treatment group but this information will not be available to the prescribing physician or the patient.

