### Intervention

The intervention consists of an IVRS call coupled with pharmacist support. We will program the IVRS to call patients automatically on day 3 and day 17 following their prescription. If a call is not answered, the system will make as many as eight separate attempts (two per day over a maximum of 4 days) before marking the call as unsuccessful. If a call is answered, the IVRS will proceed through a calling algorithm. The following questions will be asked at each call:Since receiving your medication, have you started taking it?Since receiving your medication, have you had any problems?Since receiving your medication, have you developed any new symptoms?Would you like to speak to a pharmacist?

If the patient answers ‘No’ to the first question or ‘Yes’ to any of the three remaining questions, the IVRS will inform the patient that a pharmacist will personally contact them within 2 business days. The IVRS will send an email to a pharmacist informing them of the patient’s request. In addition, the IVRS will be capable of receiving inbound calls from patients regarding their medications at any time. This will also connect the patient to the pharmacist according to the same business rules as for the outbound IVRS calls.

When required, the pharmacist will contact the patient. Prior to contact, the pharmacist will access the electronic health record to obtain background information on the patient’s health status and medication use. During the call, the pharmacist will document the patient’s problems as well as their recommendation for resolving the problem in the electronic health record. If the pharmacist deems the patient’s problems are significant, then the pharmacist can escalate the issue to the patient’s primary care physician using the electronic health record.

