### Blinding

Due to the nature of the study, blinding of patients and health-care providers will not be possible. However, we will blind personnel performing the interviews and physicians performing the assessment of ADE status of study group allocation.

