This is an ambitious study, which will run in over 100 primary care practices in two large urban settings. It will take 3 years to complete the recruitment and follow-up. We are randomizing patients at the patient rather than provider level because there is little risk of contamination or co-intervention. The patients are unlikely to interact with each other, and, based on our pilot study, there was very little interaction between patients and doctors within the 3 weeks of their prescription. There are some sources of bias in our design to be considered. The primary risk is the lack of blinding in patients and primary care doctors. This is a concern as knowledge of allocation could change behavior. However, based on findings from our pilot study, we predict this is unlikely. In addition, outcome assessment is done objectively or by blinded reviewers. In short, this study will have internal validity and will be generalizable.

In summary, we have previously developed an automated outreach program for patients prescribed new medications. We have tested this intervention in a pilot study. This work found the intervention to be feasible and suggested it might improve the quality of patient care through reduced ADE duration and improved medication adherence. We have designed this randomized trial to test whether the intervention is effective compared to routine care. If the ISTOP-ADE system were demonstrated to be effective, then there would be significant opportunities to implement this intervention through health systems, health insurance agents and commercial pharmacies.

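### A single, published block size of four within each practice can make some upcoming allocations guessable to the recruiting physician, and the statements on masking need reconciling

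*Protocol article*

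**What the plan says.** All references are to the protocol article.

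- **Randomization.** Individual patients are allocated by a computer algorithm: "We will perform stratified randomization at the physician practice level with block sizes of four". On timing: "We will only randomize patients once a physician confirms the patient’s eligibility for enrolment". The system is then updated with the group, but "this information will not be available to the prescribing physician or the patient".
- **Blinding.** "Due to the nature of the study, blinding of patients and health-care providers will not be possible". The Discussion repeats this: "The primary risk is the lack of blinding in patients and primary care doctors".
- **Who selects patients.** Under Participants: "We will exclude patients if their physicians do not deem them appropriate for study inclusion". Under Eligibility assessment and consent, the same physician tells the patient about the study, confirms eligibility and asks for consent. Reasons for ineligibility or refusal are recorded with a standard classification.
- **What the physician may see afterwards.** Under Intervention, when a pharmacist contact takes place, "the pharmacist will document the patient’s problems as well as their recommendation for resolving the problem in the electronic health record". The pharmacist may also escalate a problem to the primary care physician through that record. The control arm is routine care.

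**The concern.** Allocating by computer after eligibility is confirmed hides the current patient's allocation. It does not stop someone from inferring it from earlier patients in the same block. The stratum is the practice, so the person deciding whom to enrol may also have seen what happened to the practice's previous patients. With one block size, stated in print, each earlier allocation that becomes known changes the odds for the next.

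There is room to act on such a guess. Exclusion rests on the physician's judgement, and the Sample size section expects only half of those approached to enrol. The primary comparison is a simple chi-square test, with logistic regression only as a sensitivity analysis, so a selection imbalance would enter the main result unadjusted. The Discussion answers the lack of blinding by pointing to objective or blinded outcome assessment. That addresses detection bias, not selection at entry.

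The masking statements also do not sit easily together. One says the group is not available to physician or patient; two others say that neither is blinded. How guessable the next allocation is depends on which describes practice.

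**Working it through.** The protocol gives no figure for predictability, so there is none to reproduce.

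**Inputs from the protocol.** Blocks of four within practice (Randomization); equal arms and 2,200 patients (Sample size); over 100 practices (Discussion); 3 years of enrolment (Timeline). **Assumed:** the chance *q* that a physician learns of an intervention patient before the next enrolment.

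**1. Upper bound: all earlier allocations in the practice known.** A block has six equally likely sequences. The best guess is the arm with more places left.

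- Place 1: 1/2 correct.
- Place 2: 2/3 correct, since two of the three remaining places belong to the other arm.
- Place 3: the first two agree in 2 of 6 sequences, which makes it certain; otherwise it is a coin toss. 2/6 × 1 + 4/6 × 1/2 = 2/3.
- Place 4: always certain.

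Correct: (1/2 + 2/3 + 2/3 + 1)/4 = 17/24 = 70.8%. Certain: (1/3 + 1)/4 = 1/3.

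**2. Partial knowledge.** Suppose the physician learns of each intervention patient with probability *q*, never learns directly that a patient is a control, knows the place in the block, and guesses as well as possible. For *q* up to 0.5 the chances of a correct guess at places 1 to 4 are 1/2; 1/2 + q/6; 1/2 + q/3 − q²/6; and 1/2 + q/2 − q²/2. Their mean is 1/2 + q/4 − q²/6. An allocation is certain only once both intervention patients in the block have been noticed: probability q²/6 at place 3 and q²/2 at place 4, a share of (q²/6 + q²/2)/4 = q²/6.

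| q | Correct | Certain |
|---|---|---|
| 0 | 50% | 0% |
| 0.10 | 0.5 + 0.025 − 0.0017 = 52.3% | 0.2% |
| 0.25 | 0.5 + 0.0625 − 0.0104 = 55.2% | 1.0% |
| 0.50 | 0.5 + 0.125 − 0.0417 = 58.3% | 4.2% |
| 1 (step 1) | 70.8% | 33.3% |

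Simulation of the same model gave 52.2%, 55.3% and 58.4% correct for the three middle rows.

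**3. Pace.** Taking 100 practices, 2,200/100 = 22 patients per practice. Three years is about 156 weeks, and 156/22 is about 7 weeks between enrolments, so a block takes about 28 weeks. The day 3 and day 17 calls to one patient are usually over before the next is enrolled, so a trace could exist in time. Against that, the physician would have to keep track of the block for half a year.

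**4. Effect of varying the block size.** Take 22 patients per practice with all earlier allocations known. Fixed blocks of four give five full blocks plus two patients: correct (5 × 2.833 + 0.5 + 0.667)/22 = 69.7%; certain (5 × 1.333)/22 = 30.3%. Simulating 3,000 practices, with a guesser who knows the possible sizes but not the one in use, gave:

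| Sizes | Correct | Certain |
|---|---|---|
| 4 | 69.7% | 30.4% |
| 4, 6 | 68.6% | 5.9% |
| 4, 6, 8 | 67.2% | 2.4% |

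**5. What a guess could do to the result (illustration only).** Suppose a physician acts on every guess, enrolling patients 5 points below average non-persistence when expecting intervention and 5 points above when expecting control. With proportion *p* correct, the arms differ by 10 × (2p − 1) points: about 0.5, 1.0 and 1.7 points for *q* = 0.10, 0.25 and 0.50, and 4.2 at the upper bound. The protocol gives no evidence that physicians would steer in this way.

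**The case against.** The strongest reply is that physicians are not given the knowledge the upper bound needs. They receive no allocation list. Control patients have routine care and leave no study trace. An intervention patient leaves a note only if a pharmacist contact is triggered, and reaches the physician actively only on escalation, so the absence of a note does not show that a patient is a control. The Discussion reports very little patient-doctor contact in the first 3 weeks in the pilot and predicts that behaviour change is unlikely. Recorded reasons for exclusion leave an audit trail. No motive for steering patients is evident in a telephone follow-up trial. Varied blocks also barely change the overall guess rate.

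Most of this stands, and it moves the estimate from the upper bound to the lower rows of the table in step 2. It does not bring the risk to zero. Record notes and escalations do not depend on a patient visit, and recorded reasons help detect selective exclusion without preventing it.

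A reader might infer that the masking statements flatly contradict each other. The text does not force that reading. The Randomization sentence can refer to the group entry in the system, which is not displayed, while Blinding acknowledges that people may infer the group from the calls. The article does not say which is meant, so clarification is still needed.

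**Conclusion.** The point holds in a limited form. One disclosed block size within practice, combined with a recruiter who judges eligibility and may learn of some earlier intervention allocations, can make some upcoming allocations guessable. With 10% to 50% of intervention patients becoming known, about 52% to 58% of guesses are right and 0.2% to 4% of allocations are certain. That range is an assumption, since the protocol gives no rate for notes or escalations. It is generous to the guesser, who is taken to know the place in the block and to guess optimally. The selection-bias risk is modest.

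A reader might infer that one third of allocations will be foreseeable, or that the primary comparison is compromised. The documents do not support either. Both need every earlier allocation in the practice to be known, and the design gives physicians no such knowledge, least of all for controls. The change is worth making because it costs almost nothing and, with a start anticipated in early 2015, can be made before enrolment.

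**What to change.** 1. Use randomly varying permuted blocks within practice, for example sizes 4, 6 and 8. Withhold the sizes from practices, and keep the new sizes out of public text until enrolment ends. On the figures above this removes most certain allocations (from about 30% to about 2% with everything known) but lowers correct guessing only from about 70% to 67%, so it is a partial remedy. The cost is one setting in the randomisation program and a slightly larger possible imbalance within a practice: at most 4 patients rather than 2 at any time, being half the largest block.

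2. Reconcile Randomization with Blinding and the Discussion. Keep the commitment that the system does not show the treatment group to the physician or the patient, because it is the main barrier to prediction. Suggested addition: *Allocation is concealed until enrolment is confirmed. The system does not display it afterwards, but patients and physicians may infer it from the intervention calls or from pharmacist contact.* The cost is one or two sentences.
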